#### Outcomes and measurement instruments

We plan to measure the following patient-relevant outcomes:
Primary outcomes:Anxiety: subjective fear/anxiety of adverse events possibly caused by surgery or anesthesia
○ Measuring instrument: numeric rating scale 0–10 (validation see [38, 39]) and surgical fear questionnaire (SFQ) [40]. The SFQ comprises 8 items reflecting different aspects of surgery-related fear (e.g., anesthesia or side effects). All items are scored on a numeric rating scale 0–10. It is validated in adult patients scheduled for an elective surgery.○ Measure: meanNocebo-effect: patient reported adverse events (e.g., headache after anesthesia)
○ Measuring instrument: a questionnaire will be developed. We will use closed simple-choice questions (yes/no) to detect frequent adverse events and open-ended questions to detect other (less common) adverse events.○ Measure: proportion of patients with complications or adverse eventsSecondary outcomes:Knowledge or risk perception: questions for knowledge about benefits and risks
○ Measuring instrument: objective knowledge questions (e.g., correct risk assessment) derived in the development phase. The development will be based on previous experiences with the measure of informed choice [33, 34].○ Measure: proportion of correctly answered questionsSatisfaction with the physician-patient-communication and informed consent form
○ Measuring instrument: numeric rating scale 0–10 (validation see [41])○ Measure: meanQuality of life (QoL)
○ Measuring instrument: numeric rating scale 0–100 (validation see [42])○ Measure: meanPain and function
○ Measuring instrument: Oxford Knee Score (OKS) [43]. The OKS is a 12-item questionnaire with five scoring categories (validation see [43]).○ Measure: mean

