### Participant timeline

Table 1 depicts the participant timeline. The study includes a pre-interruption and post-interruption-phase. Participants in the pre-phase will receive informed consent based on standard consent forms (control) while participants in the post-phase will receive informed consent based on the newly developed evidence-based consent forms (intervention). Irrespective of the phase, all participating patients will follow the same study flow: study enrollment of each patient will take place approximately 4 weeks before surgery. They will receive informed consent procedures for TKA approximately 2–4 days before surgery. The informed consent procedure for anesthesia takes place approximately 4 weeks or 2–4 days before surgery, depending on the patients’ morbidity and the flexibility in scheduling. Outcomes will be measured at four specific time points for each patient: at the day of enrollment, 1 day before surgery, 3 days and 30 days after discharge from hospital.

**Table 1 Tab1:** Participant timeline (SPIRIT figure)

	Study period (25 months)													
		Pre-phase						Interruption	Post-phase					
	Time-point	4 weeks before surgery	2–4 days before surgery	1 day before surgery	Surgery	3 days after discharge	30 days after discharge		4 weeks before surgery	2–4 day before surgery	1 day before surgery	Surgery	3 days after discharge	30 days after discharge
**Enrolment**	**Eligibility screen**	X							X					
	**Informed consent**	X							X					
**Control**	**Standard consent form anesthesia**	X^a^	X^a^											
	**Standard consent form TKA**		X											
**Intervention**	**Evidence-based consent form anesthesia**								X^a^	X^a^				
	**Evidence-based consent form TKA**									X				
	**Surgery**				X							X		
**Assessments**	**Patient characteristics**	X							X					
	**Baseline anxiety**	X							X					
	**Anxiety**			X							X			
	**Health knowledge**			X							X			
	**Satisfaction with physician-patient-communication**			X							X			
	**Nocebo-effect**					X							X	
	**Quality of Life**						X							X
	**Pain and function**						X							X

^a^Informed consent for anesthesia takes place approximately 4 weeks or 2–4 days before surgery, depending on the patients’ morbidity and the flexibility in scheduling

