#### Statistical model

We will report baseline characteristics of the study population and outcomes descriptively.

We will use an ITS analysis to determine level and slope changes after the implementation of the evidence-based informed consent forms. We will use segmented regression models for our analysis. The basic model is *Y*_*t*_ = *β*_0_ + *β*_1_*T*_*t*_ + *β*_2_*X*_*t*_ + *β*_3_(*T* − *T*_0_)*X*_*t*_

*X*_t_ is a dummy which differentiates pre- and post-intervention periods. *T* is the time since the start of the study in months. β_0_ is the base level. β_1_ is the course of the slope before the implementation of the intervention. β_2_ is the level change, which describes the immediate effect on *Y* after the implementation of intervention *X*. β_3_ is the course of the slope after the implementation of the intervention, whereby *T*_o_ is the time of beginning of the study. We will use negative-binomial regression models for all count data (nocebo effect and objective knowledge questions) and generalized linear model for outcomes which can be analyzed as continuous variables (anxiety, satisfaction, quality of life, OKS).

We will create two models. One model will analyze the intervention as a complex package of measures on hospital level. The intervention effect will be analyzed on the hospital level. We will adjust the analysis for potential unforeseen time-varying confounders (e.g., changes of the standard consent form by hospital information policies, structural changes in consent because of corona pandemic). Potential confounders for each outcome will be identified based on visual inspection of trajectory curve and content-related thinking. We will assess autocorrelation by examining the plot of residuals.

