In a second model, we will analyze the intervention effect on an individual level. This means, the study is analyzed as historical cohort study. In this model, the individual intervention components (informed consent forms, parallel performance of informed consent by orthopedic and aesthetic medical staff, participation on the training for evidence-based decision-making) are modelled as separate intervention components. We will perform this exploratory analysis to get insights into the isolated effect of evidence-based informed consent forms and interaction effects with other intervention components. We will adjust the models for baseline characteristics (age, sex, educational level, and marital status) and a potential time trend (since the comparison group is a historical control).

In case > 5% of data for an outcome are missing, we will impute the missing data by multiple imputation using the Markov chain Monte Carlo method. In addition to this primary analysis, we will perform a best-case/worst-case analysis to assess the robustness of results depending on missing data [48].

To quantify the statistical uncertainty, the associated 95% confidence intervals will be provided for all effect estimates. As we will conduct an explorative pilot study, we will not perform a test for statistically significant differences. We will prepare interrupted-time-series graphs to visualize the results [49].

All analyses will be performed using SAS software [50] and R [51].

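### The individual-level model fixes a covariate list that omits baseline anxiety, although the study collects it from every patient and anxiety is a primary outcome

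*Protocol article*

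**What the plan says.** All references are to the protocol article.

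- **Outcome.** Outcomes and measurement instruments names anxiety as a primary outcome, defined as "subjective fear/anxiety of adverse events possibly caused by surgery or anesthesia". It is measured on a 0–10 rating scale and with the Surgical Fear Questionnaire and summarised as a mean. Statistical model places it among the outcomes treated as continuous.
- **Schedule.** Participant timeline states "Irrespective of the phase, all participating patients will follow the same study flow". Measurements are taken "at the day of enrollment, 1 day before surgery, 3 days and 30 days after discharge from hospital". Table 1 marks "Baseline anxiety" at four weeks before surgery and anxiety again one day before surgery, in both phases.
- **Individual-level model.** Statistical model describes a second, exploratory analysis that treats the study as a historical cohort. Its adjustment is stated as: "We will adjust the models for baseline characteristics (age, sex, educational level, and marital status) and a potential time trend". The list is not introduced as a set of examples. No change score or other use of the baseline anxiety value is described.
- **Hospital-level model.** The same section does not fix the confounders of the first, primary model. They are to be chosen outcome by outcome, from the trajectory plots and subject-matter reasoning.
- **Anaesthesia consent.** Participant timeline puts it at about four weeks or at 2–4 days before surgery, "depending on the patients’ morbidity and the flexibility in scheduling".
- **Design risk.** Limitations acknowledges confounding bias and gives a pandemic example in which the kind of patient operated on changes.

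**The concern.** In a non-randomised before/after comparison, the pre-exposure value of the outcome shows most directly whether the two groups already differed on that outcome. It is often also the strongest single predictor of the later value. Education and marital status are weak substitutes for it. Here the score is collected from everyone, but the one model with a stated covariate list leaves it out.

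Two things are at stake for the individual-level anxiety estimate:

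- **Precision.** The study plans confidence intervals and no tests, so interval width is its main inferential output.
- **Confounding.** If patients in one phase arrive more anxious, for example because a pandemic restriction abruptly changes who is operated on, part of that difference is read as an effect of the consent forms.

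The pilot is also meant to supply planning figures for a definitive trial. A residual variance after baseline adjustment would be directly useful for that.

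**Working it through.** **1. The plan's own figure.** Sample size plans 220 participants with 10% dropout: 220 × 0.90 = 198. The chance of seeing at least once a problem with 2% probability is 1 − 0.98^198 = 0.982, which agrees with the stated 98%. This figure does not depend on the analysis model, so nothing below alters it.

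**2. Inputs for the check.**
- Analysed participants: 198, or 99 per phase (Sample size, equal allocation).
- Correlation r between baseline anxiety and anxiety the day before surgery: not in the article. Assumed 0.3, 0.5 and 0.7. Strictly, this is the correlation left after the covariates already in the model.
- Baseline imbalance d between phases: not in the article. Assumed 0.2 SD.
- SD of anxiety: assumed equal at both times.

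**3. Precision.** Adding the baseline value multiplies the residual variance by 1 − r² and the standard error by √(1 − r²). The equivalent unadjusted sample is 198 / (1 − r²).

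| r | 1 − r² | SE ratio | SE reduction | Equivalent unadjusted n |
|---|---|---|---|---|
| 0.3 | 0.91 | 0.954 | about 5% | 218 |
| 0.5 | 0.75 | 0.866 | about 13% | 264 |
| 0.7 | 0.51 | 0.714 | about 29% | 388 |

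**4. Bias.** An abrupt baseline difference d that is not adjusted for carries over as slope × d, where slope = r × SD(outcome) / SD(baseline). With equal SDs this is r × d:
- r = 0.3: 0.3 × 0.2 = 0.06 SD
- r = 0.5: 0.5 × 0.2 = 0.10 SD
- r = 0.7: 0.7 × 0.2 = 0.14 SD

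**5. Simulation check.** 2,000 data sets per setting were generated with 99 patients per phase over 12 + 12 months. Each was fitted with a phase term and a linear time trend, with and without the baseline value. This is a simplified version of the second model: one phase indicator, no separate intervention components and none of the four listed covariates.

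| r | SE without baseline | SE with baseline | Ratio | Bias without (d = 0.2) | Bias with (d = 0.2) |
|---|---|---|---|---|---|
| 0.3 | 0.285 | 0.272 | 0.956 | 0.061 | 0.002 |
| 0.5 | 0.286 | 0.248 | 0.867 | 0.090 | −0.007 |
| 0.7 | 0.285 | 0.204 | 0.716 | 0.144 | −0.001 |

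SEs and biases are in SD units. The SE columns are from the runs with d = 0. The simulation agrees with the formulas.

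**6. Scale.** Set against the unadjusted SE of 0.285 SD, the formula bias is 0.06 / 0.285 = 0.21, 0.10 / 0.285 = 0.35 and 0.14 / 0.285 = 0.49 of one standard error. That is noticeable but not dominant.

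**The case against.** Several limits on this point are sound.

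- **The model is exploratory.** The closed list belongs to a secondary model in a pilot without significance tests. This stands and lowers the stakes. It does not explain why a score already collected is left out.
- **The primary model is not shown to omit the score.** A reader might infer that no analysis uses baseline anxiety. The article does not support that: confounders in the hospital-level model are left open for each outcome, and baseline anxiety could be chosen there.
- **The time trend does some of the work.** A reader might infer that any change in case mix passes straight into the effect. It does not. Gradual drift would be absorbed at least in part by the trend term, and the bias figures above are for an abrupt shift at the changeover.
- **The correlation is unknown.** At r = 0.3 the gain is small. This stands, and it is why the range starts there.
- **Morbidity.** Because anaesthesia-consent timing depends on "morbidity and the flexibility in scheduling", a reader might infer that morbidity confounds the joint-consent component and should simply be added. The article does not say that morbidity is recorded, it names scheduling as well, and the link from timing to joint consent is an inference. This is not an unused covariate that the study already holds.
- **Order at the four-week visit.** The article does not say whether baseline anxiety is asked before an anaesthesia form that may be given at the same time point. Such detail belongs in the interviewer manual, which is not shown, so its absence is no fault. It matters only as a condition on using the score as a covariate.

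**Conclusion.** The point holds for the individual-level anxiety models. Their stated covariate list leaves out the baseline value of a primary outcome that is scheduled for every patient, in a historical comparison for which the authors themselves anticipate confounding. A protocol may leave covariates to an analysis plan, but this one states a specific list, and the list is poorly chosen for this outcome.

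The cost is a standard error larger than it need be: adjustment would lower it by about 5% to 29% for r between 0.3 and 0.7. There is also an avoidable bias of about 0.06 to 0.14 SD if the phases differ abruptly by 0.2 SD at baseline. Both ranges rest on assumed values of r and d, and the bias also on equal SDs at the two times.

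The finding does not extend to the primary hospital-level model, and no sample-size statement is wrong.

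**What to change.** In Statistical model, add baseline anxiety to the covariates of the individual-level models for the anxiety outcomes, pairing each outcome with its baseline on the same instrument (rating scale with rating scale, fear questionnaire with fear questionnaire). The article does not say which instrument is used at baseline, so this should be confirmed.

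State that the baseline used is taken before any consent form is handed over. For patients whose anaesthesia consent falls at the four-week time point, a score taken after the form would already carry part of the effect, and adjusting for it could remove that part.

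For the hospital-level model, monthly mean baseline anxiety may be named as a candidate confounder for the anxiety outcome. This is optional, since that model's list is open.

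The cost is a sentence in the plan, one term in the code and a confirmed question order at enrolment. If the instruments already match, no new data item is needed, and the sample size does not change.

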#### Methods: monitoring

Due to the nature of the intervention, there will be no data monitoring committee.

#### Sub-study IV: process evaluation

Following the Medical Research Councils process evaluation framework for complex interventions [52], we will plan and conduct the process evaluation. The detailed planning will be based on the results of the sub-studies I and II. We will describe the intervention, its casual assumptions and the implementation process. We will analyze the contextual factors and the mechanisms of impact such as participant responses and mediators. The legal framework of informed consent will always be considered. Mixed methods will be applied to assess intervention fidelity and the processes and mechanisms on different levels. The informed consent process will be documented on a standardized form (e.g., duration, orthopedist and anesthetist together, new informed consent form used yes/no, consent provided yes/no). The context will be explored using the Practice Adaptive Reserve Scale [53]. The model of adaptive reserve considers external factors as well as leadership, learning culture, teamwork, or characteristics of the relationships in the work environment. Readiness to change on a healthcare professional level will be surveyed using the German Version of the Change Attitude Scale [54]. The Change Attitude Scale is a three-dimensional tool, measuring the affective (how people feel about the change), cognitive (what people think about the change), and behavioral (behavior in response to the change) dimension. Barriers and facilitators of implementation will be explored using qualitative methods. We will perform semi-structured interviews with patients and physicians. Participating orthopedists and anesthetists who regularly perform informed consent procedures and a random sample of patients in the intervention group (20% of participants) will be included. The selected patients will be contacted by telephone approximately 1 month after informed consent. At the end of the study, personal interviews with the physicians will be scheduled if possible. Otherwise, they will also be contacted by telephone. The interviews will be audio recorded and transcribed. Qualitative content analyses will be performed [20]. A descriptive analysis will be performed on the quantitative data.

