#### Blinding

Standard consent forms and evidence-based informed consent forms are obviously different. Therefore, blinding of medical staff will be impossible. We will not explicitly inform participants about receiving a “different” informed consent form but only about the nature of the study. The statistical analysis will be performed blinded.

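### Process-evaluation interviews, held in the intervention group only, are timed before the 30-day quality-of-life and Oxford Knee Score assessments and could influence these two secondary outcomes (minor)

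*Protocol article*

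**What the plan says.** The protocol article, under Sub-study IV: process evaluation, selects for interview the participating physicians and, among patients, "a random sample of patients in the intervention group (20% of participants) will be included". The purpose is stated: "Barriers and facilitators of implementation will be explored using qualitative methods". The date is also stated: "The selected patients will be contacted by telephone approximately 1 month after informed consent". The section does not say which consent starts the month, or where the call stands in relation to the outcome surveys.

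The Participant timeline section gives the other dates:

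- Enrolment: "study enrollment of each patient will take place approximately 4 weeks before surgery".
- Consent for the operation: "They will receive informed consent procedures for TKA approximately 2–4 days before surgery".
- Consent for anesthesia: "The informed consent procedure for anesthesia takes place approximately 4 weeks or 2–4 days before surgery".
- Outcomes after enrolment: "1 day before surgery, 3 days and 30 days after discharge from hospital".

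Table 1 assigns anxiety, knowledge and satisfaction to the day before surgery, the nocebo outcome to 3 days after discharge, and only QoL and OKS to 30 days after discharge. The same section states that patients in both phases go through an identical flow. The Blinding section says of the forms: "We will not explicitly inform participants about receiving a" form that differs from the usual one.

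**The concern.** In a before–after comparison, anything that happens only in the post-phase before an outcome is recorded becomes part of the estimated phase effect. A telephone conversation about the consent process is such a contact. It adds attention, it returns the patient to the consent material, and it may let the patient infer that the form was new, which the study has chosen not to announce. If it precedes QoL and OKS in some intervention patients and in no controls, the contrast for those outcomes combines the form and the interview.

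The planned analysis does not separate the two. The hospital-level segmented regression has one level change and one slope change. The individual-level model separates the forms, joint consent by the two specialties, and training; the interview is not among its components. The pilot is also meant to supply planning data and expose process problems for a definitive trial, so a contact schedule of this kind could be carried forward.

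**Working it through.** **Inputs from the article.** TKA consent on day −4 to −2 (surgery = day 0). Enrolment, and sometimes anesthesia consent, at about day −28. Outcomes on day −1, at discharge + 3 and at discharge + 30. Planned size 110 per phase, with 10% dropout leaving 198, or 99 per phase.

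**Assumptions.** One month = 28–31 days. Length of stay L is not given, so a range of 0–14 days is used.

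**1. The article's own planning figure.** 220 × 0.90 = 198, and 1 − 0.98^198 = 0.982, which agrees with the stated 98%. The present point does not depend on this figure; only the 99 per phase is used below.

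**2. Date of the interview, counted from TKA consent.** Earliest: −4 + 28 = day 24. Latest: −2 + 31 = day 29.

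**3. Date of QoL and OKS.** Day L + 30. The lead of the interview is (L + 30) − 29 to (L + 30) − 24, that is L + 1 to L + 6 days:

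| Stay L (assumed) | QoL/OKS on day | Interview earlier by |
|---|---|---|
| 0 | 30 | 1–6 days |
| 7 | 37 | 8–13 days |
| 14 | 44 | 15–20 days |

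The order reverses only if calls slip. At 35 days after consent the interview is on day 31–33, which is later than the assessment only for stays of about 0–2 days. At 42 days it is on day 38–40, which is later only for stays up to about 7–9 days.

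**4. The other outcomes, on the same count.** Anxiety, knowledge and satisfaction are recorded on day −1. The nocebo report is on day L + 3, that is day 3–17, and stays before day 24 for any stay up to 20 days. None of these is exposed.

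**5. If the month runs from a consent about 4 weeks before surgery.** Interview on day −28 + 28 = 0 to −28 + 31 = 3. The lead over QoL and OKS is 27–44 days. The nocebo report on day L + 3 would then follow the interview in almost all cases (same day at the extreme of L = 0 and a 31-day month). Anxiety on day −1 would still come first on the nominal schedule.

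**6. Reach and size.** 0.20 × 110 = 22 patients. If 20% refers to all participants, 0.20 × 220 = 44, which is 44/110 = 40% of the phase. An average effect d among those interviewed shifts the intervention mean by 0.2d or 0.4d. The article gives no value of d, so a range is assumed:

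| d (SD, assumed) | Shift at 20% | Shift at 40% |
|---|---|---|
| 0.1 | 0.02 | 0.04 |
| 0.2 | 0.04 | 0.08 |
| 0.5 | 0.10 | 0.20 |

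For scale, a simple 99 v 99 comparison has SE = √(2/99) = 0.142 SD and a 95% half-width of 1.96 × 0.142 = 0.28 SD. Every shift in the table lies inside that half-width.

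**The case against.** The strongest reply has four parts.

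**The primary outcomes are untouched.** A reader might infer that the interviews contaminate the trial's outcomes in general. The documents do not support this. In the process-evaluation section, informed consent most naturally means the clinical procedure carried out by orthopedists and anesthetists. Counted from TKA consent, anxiety, knowledge, satisfaction and the nocebo report are all collected before the call. The route to the nocebo outcome requires the month to start about 4 weeks before surgery, which would place the call around the operation, when some patients would barely have had the TKA form. That is an unlikely plan. It cannot be ruled out entirely: Table 1 uses the label for study consent at enrolment, and anesthesia consent may also take place at that time.

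**No effect is shown.** A reader might also infer that the interview does change QoL or OKS, or that it prompts patients about risks and reveals the comparison. The article gives no question guide and no evidence that one qualitative call alters a quality-of-life rating or a knee score. Direction and size are unknown. This part stands: the influence is possible, not demonstrated.

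**The size is small.** This is an exploratory pilot with confidence intervals and no significance tests, and the dilution to 20% (or 40%) keeps plausible shifts inside the interval. This also stands, and it limits the weight of the point.

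**Detail is deferred.** The article says that detailed planning of the process evaluation will build on sub-studies I and II, and it is a condensed account. This does not dispose of the matter, because the timing is not left open. It is stated, and as stated it places the call before the last assessment.

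**Conclusion.** The point holds in a limited form. On the stated schedule the interview precedes QoL and OKS under every reading of which consent starts the month. From TKA consent the lead is L + 1 to L + 6 days. It reaches about a fifth of one phase (two fifths on the wider reading of the 20%) and nobody in the other, which departs from the identical flow that the timeline describes.

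What is at risk is the interpretation of two secondary outcomes, by 0.2d or 0.4d. With d up to an assumed 0.5 SD that is at most 0.10 or 0.20 SD, against a half-width of about 0.28 SD. The conclusion about order rests on calls being made close to one month; a slip to five or six weeks combined with a short stay would reverse it. The conclusion about size rests on assumed values of d and on a simple two-group comparison rather than the segmented model. The weight is minor: an avoidable asymmetry that is cheap to remove.

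**What to change.** In the process-evaluation section, state which consent starts the interval, and hold each sampled patient's interview until that patient's 30-day assessment is complete (at the end of the same call, or in the days after). Say also whether 20% refers to the intervention group or to all participants.

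The cost is a sentence or two and a longer recall period: roughly one to two weeks for a stay of about a week, and up to about three weeks at the upper end of the assumed range. No outcome assessment moves.

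If the calls cannot move, add a sensitivity analysis of QoL and OKS that leaves out every patient drawn for interview, not only those who were reached. Because the draw is random, this removes the contact without selecting patients. With dropout spread evenly, it leaves 99 × 0.8 ≈ 79 intervention patients. The half-width of the simple comparison becomes 1.96 × √(1/79 + 1/99) ≈ 0.30 SD instead of 0.28. At 40% it leaves 99 × 0.6 ≈ 59, and about 0.32 SD.
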